## Definition of MTD

Within 25 days after the first dose, if ≤ 1 DLT occurs among 6 subjects, the highest dose that meets this criterion will be defined as the MTD. If all dose groups specified in the protocol have been completed and no DLT occurs in the highest dose group, then the highest dose will be determined as the MTD.

## Dietary and Lifestyle Restrictions

### Diet

During the single-dose and multiple-dose phases, subjects should avoid consuming foods or beverages containing caffeine (such as tea, coffee, cola, etc.), xanthines (such as chocolate), and grapefruit. Smoking and alcohol consumption are prohibited throughout the entire trial.

Subjects will be admitted to the ward the day before the PK study and will remain there until 24 hours after the PK blood samples are collected post-dosing. The investigational drug will be administered to subjects in the morning on the day of the trial, following an overnight fast (at least 10 hours) for fasting administration. A light meal may be provided 2 hours after dosing, with lunch approximately 4 hours after dosing and dinner approximately 10 hours after dosing; thereafter, normal meal times may resume. Fluid intake will be controlled for 1 hour before dosing and for 2 hours after dosing, with no restrictions on fluid intake during other times, while avoiding drinks containing caffeine such as coffee, tea, and cola. Subjects should refrain from vigorous exercise during the trial. When blood collection time points overlap with meal or examination time points, blood collection will be performed first, followed by the examination, and then the meal.

### Contraception

Male participants (and their female partners) as well as female participants of childbearing potential should use reliable contraception from the first dose of the study drug until six months after the last dose (see Appendix 14.9)

# Trial Population

## Sample Size

This trial is provisionally set to include 7 dosage groups, with a planned enrollment of 21-42 participants primarily consisting of patients with B-cell-related tumors in the category of relapsed or refractory hematologic malignancies.

## Definition of the Trial Population

The specific definition of relapsed or refractory hematologic malignancies primarily involving B-cell-related tumors is referenced as follows. For diseases not specifically defined in this section, the investigator will determine them according to the latest guidelines for each condition:

- 1. **B-cell lymphoma and T-cell lymphoma**

According to the "Guidelines for the Diagnosis and Treatment of Diffuse Large B-Cell Lymphoma in China (2013 Edition)" and recent clinical studies of newly marketed drugs, relapsedor refractory B-cell lymphoma and T-cell lymphoma are defined as follows (may not apply to certain rare or currently non-research hotspot pathological types):

- RelapsedB-cell lymphoma and T-cell lymphoma: Refers to disease progression after adequate treatment achieving remission (including PR and CR).

Disease progression is indicated by the appearance of any new lesions or an increase in the diameter of existing lesions by ≥ 50%, including but not limited to the following situations: (1) Lymphadenopathy: The appearance of any new lesion with a diameter > 1.5 cm; an increase of ≥ 50% in the sum of the products of the maximum vertical diameters of multiple lesions; or an increase of ≥ 50% in the maximum diameter of a single lesion with a short axis > 1 cm before treatment. Additionally, lesions that were FDG avid or PET positive before treatment and are PET positive after treatment. (2) Spleen and liver: An increase of ≥50% in the sum of the products of the maximum vertical diameters of any lesions. (3) New or relapsedbone marrow involvement.

- Refractory B-cell lymphoma and T-cell lymphoma: Defined as meeting any of the following criteria: (1) Disease progression after two cycles of standard regimen chemotherapy, or failure to achieve remission (including PR and CR) after four cycles of treatment; (2) Achieving CR after standard regimen chemotherapy, followed by relapse within 6 months; (3) Two or more relapses after achieving CR; (4) Relapse after hematopoietic stem cell transplantation.
  1. **B-cell acute leukemia and T-cell acute leukemia (collectively referred to as acute lymphoblastic leukemia, ALL)**

According to the "Guidelines for the Diagnosis and Treatment of Adult Acute Lymphoblastic Leukemia in China (2016 Edition)" and the National Comprehensive Cancer Network (NCCN) guidelines, relapsedor refractory acute lymphoblastic leukemia in adults is defined as follows:

- RelapsedALL: The reappearance of blasts in peripheral blood or bone marrow (proportion > 5%) after achieving complete remission (CR) following induction therapy, or the presence of extramedullary leukemia.
- Refractory ALL: Defined as meeting any of the following criteria: ① Failure to achieve CR with a standard 4-week induction therapy regimen, and no response after an additional two weeks of chemotherapy. ② Relapse within 6 months of the first remission, classified as early relapse. ③ Relapse more than 6 months after the first remission, but failure of retreatment with the original induction regimen. ④ Multiple relapses (relapse ≥ 2 times).
  1. **Multiple Myeloma（MM）**

According to the "Chinese Guidelines for the Diagnosis and Treatment of Multiple Myeloma (2017 Revision)" and the definition provided by the International Myeloma Working Group (IMWG) in 2016, relapsed or refractory multiple myeloma is defined as follows:

- Relapsed multiple myeloma (MM) refers to patients who have previously achieved at least a minimal response (MR) or better following treatment but then experience disease progression, necessitating the initiation of salvage therapy. It is categorized into clinical relapse and relapse after complete response (CR).

Clinical relapse is defined as meeting at least one of the following criteria: (1)The appearance of new bone lesions or soft tissue plasmacytomas (excluding osteoporotic fractures); (2)A clear increase in existing plasmacytomas or bone lesions (an increase of 50% in the sum of the products of the maximum vertical diameters of measurable lesions, with an absolute value of ≥1 cm); (3)Hypercalcemia; (4) A decrease in hemoglobin of≥20 g/L (unrelated to treatment or non-MM factors); (5)An increase in serum creatinine of≥176.8 µmol/L that is related to MM since the start of MM treatment; (6) Hyperviscosity syndrome related to serum M-protein.

Relapse after complete response (CR) is defined as meeting any of the following criteria: (1)The reappearance of serum or urine M-protein confirmed by immunofixation electrophoresis; (2) A bone marrow plasma cell percentage of ≥5%; (3) Any other signs of progressive disease (PD).

- Refractory Multiple Myeloma (MM) is categorized into primary refractory and relapsed refractory.

Primary Refractory: This is defined as the lack of response to any treatment, where the patient has not achieved at least a minimal response (MR). This includes cases where the disease does not respond to treatment but has not progressed, as well as cases where the disease does not respond to treatment and progresses.

Relapsed Refractory: This refers to patients who had previously achieved at least a minimal response (MR) or better following treatment but then experience disease progression. In this case, after salvage therapy, there is no response, or the disease progresses within 60 days of the last treatment.

## Grouping

Once participants have signed the informed consent form and undergone screening, they will receive a three-digit screening number in the order of their screening, such that the first participant to sign the consent and undergo screening will have a screening number of 001. Eligible participants will be assigned a three-digit enrollment number based on the order of their enrollment, with the first enrolled participant receiving an enrollment number of 001. In cases where a participant needs to be replaced, the replacement participant will be assigned a new enrollment number in accordance with the order of enrollment.

## Inclusion Criteria

1. Age between 18 and 70 years, regardless of gender.
2. Diagnosis confirmed by histopathological or cytological examination (according to the "Diagnostic Criteria and Efficacy Standards for Hematological Diseases" (4th Edition) published by Science Press) for hematological malignancies, including but not limited to B-cell lymphoma, multiple myeloma, B-cell acute leukemia, T-cell lymphoma, and T-cell acute leukemia. Patients must have experienced disease progression, relapse, or be unsuitable for standard treatment after receiving standard treatment regimens (specific definitions for relapsed or refractory disease can be found in Section 4.2).
3. No severe organic lesions in the heart, lungs, liver, or kidneys (LVEF≥50%; total bilirubin ≤1.5×ULN; ALT ≤1.5×ULN; AST ≤1.5×ULN; serum creatinine ≤1.5×ULN or CCr > 40 mL/min).
4. No severe coagulation dysfunction (PT≤1.5×ULN, APTT≤1.5×ULN, TT≤1.5× ULN, and FIB≥1.0 g/L).
5. No severe hematological abnormalities (absolute neutrophil count≥1.5×10^9^/L, platelets≥75×10^9^/L, hemoglobin≥80 g/L), and no transfusion of platelets, red blood cells, or hemoglobin within the 2 weeks prior to screening.
6. At least 4 weeks or more than 5 half-lives since the last anti-tumor treatment (chemotherapy, radiotherapy, biological therapy, or immunotherapy) prior to enrollment.
7. Expected survival time of≥12 weeks.
8. ECOG performance status of≤2.
9. Willingness to participate in the study and sign the informed consent form.

## Exclusion Criteria

1. Toxicity Recovery: Patients whose prior cancer treatment-related toxicities have not recovered to Grade I or below, or who have not fully recovered from previous surgeries.
2. Severe Chronic Diseases: Patients with severe lung, liver, kidney, gastrointestinal diseases, or chronic diseases of major organs.
3. Pregnancy and Lactation: Pregnant or breastfeeding women, and patients of childbearing potential who refuse to use contraception during the trial.
4. Recent Cardiac Events: History of acute myocardial infarction, congestive heart failure (NYHA Class ≥ 2), unstable angina, or stroke within the past 6 months.
5. Impaired Cardiac Function: Patients with impaired cardiac function (echocardiogram showing ejection fraction < 45%, complete left bundle branch block with ST segment depression > 1 mm or T-wave inversion in two or more leads; congenital ventricular or atrial arrhythmias; clinically significant tachycardia (> 100 beats/min), bradycardia (< 50 beats/min), QTc > 450 ms (male), QTc > 480 ms (female), or clinically significant heart disease such as unstable angina, congestive heart failure, or myocardial infarction within the last 6 months).
6. CNS Involvement or Mental Disorders: Patients with central nervous system lymphoma/leukemia or significant psychiatric disorders.
7. Organ Transplant History: Patients with a history of organ transplantation.
8. Severe Active Infections: Patients with severe active infections.
9. Allergies: Known severe allergy to the study drug, its excipients, or HDAC inhibitors.
10. Viral Infections: Patients who are positive for HCV antigen or antibodies, HIV antigen or antibodies, HBsAg positive, HBcAb positive, and have peripheral blood HBV DNA levels ≥ 1 × 10^3 IU/mL.
11. Substance Abuse: Individuals with alcohol dependence or drug abuse.
12. Recent Participation in Other Trials: Patients who have participated in other drug clinical trials within the past month.
13. Other Factors: Any other factors that the investigator deems as unsuitable for participation in the trial.

## Criteria for Withdrawal from the Study

Participants have the right to withdraw from the study at any stage, and their interests will not be adversely affected by their decision to exit. If a participant requests to withdraw from the trial, study treatment must be discontinued. Additionally, if a participant does not explicitly state their intention to withdraw but ceases to take medication and undergo tests, this will also be considered a withdrawal or dropout.

If a participant decides to withdraw, all observations should be completed and reported as thoroughly as possible before exiting. A full final assessment should be conducted at the time of withdrawal, and the reason for withdrawal must be documented. If a participant withdraws due to adverse events or abnormal laboratory results, relevant details must be recorded in the case report form.

The investigator should consider early termination of the study for a participant in the event of any of the following occurrences:

1. Evidence of disease progression;
2. Appearance of intolerable toxicity leading to discontinuation of the study drug, and failure to recover within 14 days after discontinuation;
3. Poor compliance by the participant, making them unsuitable to continue in the study;
4. Serious violations of the study protocol that affect drug tolerance and safety evaluation;
5. Participant lost to follow-up;
6. Pregnancy;
7. Other reasons deemed by the investigator as making the participant unsuitable to continue in the trial.

## Subject Supplementation

Subjects who discontinue the study within 25 days after the first dose for reasons other than dose-limiting toxicities (DLTs) — such as participant withdrawal from the clinical trial, serious protocol violations, failure to meet inclusion/exclusion criteria, poor compliance, or early evidence of disease progression — may be supplemented to ensure that the number of evaluations for DLTs remains sufficient.

# Investigational Drug

## Drug Introduction

| Drug Name | Purinostat Mesylate for injection |
| --- | --- |
| Characteristics | Light yellow to off-white loose aggregate or powder |
| Active Ingredient | Purinostat Mesylate（Purinostat Mesylate）  Chemical name: 2-(((2-(4-Aminophenyl)-9-methyl-6-(4-morpholinyl)-9H-purine-8-yl)methyl)methylamino)-N-hydroxy-5-pyrimidine-carboxamide Mesylate (IUPAC)  Chemical structure :   |
| Composition | Purinostat Mesylate， Hydroxypropyl beta-cyclodextrin, arginine, glucosamine, mannitol |
| Specification | 20 mg/bottle (as Purinostat Mesylate) |
| Storage Conditions | Protect from light, store in a tightly closed container in a cool place |
| Expiration Date | Tentative shelf life of 24 months |
| Batch Number |  |
| Manufacturer | Chengdu Zenitar Biomedical Technology Co., Ltd |

## Drug Labeling

The sponsor will package the investigational drug and affix a label that includes the drug name, specification, dosage and administration, drug batch number, expiration date, storage conditions, supplying entity, precautions, and the statement "For Phase I clinical trial use only."

**Sample Drug Label**

| **Purinostat Mesylate for injection**  **（For Phase I clinical trial use only.）**  **Specification:** 20 mg/bottle  **Dosage Form:** Intravenous infusion  **Dosage:** Administer according to the specified dose group for the subject  **Drug Batch Number:**  **Expiration Date:**  **Supplying Entity:** Chengdu Zenitar Biomedical Technology Co., Ltd  **Storage Conditions:** Protect from light, store in a tightly closed container in a cool place  **Precautions:** The product should be immediately prepared into a solution after dissolution and should not be frozen. The prepared solution should be administered immediately, and the time from preparation to the end of infusion should not exceed 6 hours. |
| --- |

## Preparation Method

Prior to administration, allow each vial of lyophilized Purinostat Mesylate to reach room temperature. Once equilibrated, add physiological saline to each vial to achieve the appropriate drug concentration. Withdraw the intended dose of the diluted solution and add it to physiological saline to a total volume of 50 mL, and infuse intravenously at a constant rate over 30 minutes.

The product should be prepared into a solution immediately after dissolution and must not be frozen. The prepared solution should be administered immediately, and the time from preparation to the end of infusion should not exceed 6 hours.

## Administration Method

The designated personnel will administer the drug via an infusion pump for a constant rate intravenous infusion. The administration volume is 50 mL, and the infusion time is 30 minutes. The actual infusion time will be recorded. During the clinical trial, adjustments to the drug concentration, infusion rate, infusion time, and administration volume will be made as necessary based on the subject's safety and tolerability.

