| **Number of subjects planned to be enrolled** | It is expected that 21 to 42 patients with relapsed or refractory B-cell-related hematologic malignancies will be enrolled, including but not limited to patients with B-cell lymphoma, multiple myeloma, B-cell acute leukemia, T-cell lymphoma, and T-cell acute leukemia who have experienced disease progression, relapse, or are unsuitable for standard treatment after receiving standard therapies. |
| **Trial groups and drug dosage** | This study will adopt a modified Fibonacci method for dose escalation, with seven predefined trial dose groups:   \| **Group** \| **1** \| **2** \| **3** \| **4** \| **5** \| **6** \| **7** \| **…..** \| \| --- \| --- \| --- \| --- \| --- \| --- \| --- \| --- \| --- \| \| Incremental ratio \| Initial dose \| 100% \| 67% \| 50% \| 40% \| 33% \| 33% \| 33% \| \| Dose (mg/m^2^) \| 1.2 \| 2.4 \| 4.0 \| 6.0 \| 8.4 \| 11.2 \| 15 \| Previous dose×33% increment  （Maximum drug exposure < 36.88 mg/m^2^） \| \| Number of subjects \| 3-6 \| 3-6 \| 3-6 \| 3-6 \| 3-6 \| 3-6 \| 3-6 \| 3-6 \|   If the maximum dose defined in this protocol (15 mg/m²) does not reach the MTD, the decision to continue dose escalation will be based on pharmacokinetic (PK), pharmacodynamic (PD) indicators, and safety data. If PK or PD indicators suggest that systemic drug exposure has not yet reached saturation, dose escalation will proceed according to the modified Fibonacci method until the MTD is observed or the drug reaches sufficient exposure in the body (the maximum drug exposure should not exceed the exposure at the canine HNSTD dose, which corresponds to an equivalent human dose of 36.88 mg/m²). |
| **Preparation and method of administration** | **Preparation Method:** The drug is prepared at room temperature. Before administration, each vial of PM (specification: 20 mg/vial) is reconstituted and diluted with sterile normal saline to an appropriate concentration until fully dissolved. After preparation, it must be administered via intravenous infusion over 30 minutes.  **Administration Method:** The drug is administered using an infusion pump through a peripheral vein, with an infusion volume of 50 mL and an infusion time of 30 minutes. The actual infusion time will be recorded. During the clinical trial, adjustments may be made to the drug concentration, infusion rate, infusion time, and infusion volume based on individual subject safety and tolerability. |

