### Sample Collection Timing

Single-Dose Pharmacokinetic Study:

The PK sampling points will be adjusted based on the pharmacokinetic trial results and tolerability observed in the first patient as follows:

For each patient, blood samples of 3 mL will be collected from the antecubital vein using an indwelling needle at the following time points: within 0.5 hours before administration, and at 5 minutes, 10 minutes, 20 minutes, 30 minutes (immediately after administration), 32 minutes, 35 minutes, 45 minutes, 1 hour, 2 hours, 4 hours, 8 hours, and 12 hours after administration.

Multiple-Dose Administration Phase

D11: Blood samples of 3 mL will be collected within 0.5 hours before administration;

D15: Blood samples of 3 mL will be collected within 0.5 hours before administration, and at 5 minutes, 10 minutes, 20 minutes, 30 minutes (immediately after administration), 32 minutes, 35 minutes, 45 minutes, 1 hour, 2 hours, 4 hours, 8 hours, and 12 hours after administration.

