## Pharmacokinetic Analysis

The blood concentration-time curves for each subject will be plotted for each time point. Based on the blood concentration-time data, pharmacokinetic parameters will be calculated using the standard non-compartmental model method in the WinNonlin software. The main pharmacokinetic parameters obtained will include T_max_, C_max_, AUC_0-t_, AUC_0-∞_, t_1/2_, MRT, CL, Ke, and V. Descriptive statistics will be used to list the mean, standard deviation, median, maximum, and minimum for the continuous data.

Dose proportionality analysis will be performed using single-dose pharmacokinetic parameters (PKPS) and analyzed with a power function model to examine the relationship between AUC, C_max_, and dose. The linearity criterion will be that the 95% confidence interval for the β value includes 1.

Accumulation will be assessed by comparing Cmax and AUC_SS_ from multiple dosing with C_max_ and AUC_0-48h_ from single dosing to calculate the accumulation ratio.。

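### Infusion time may be changed for individual subjects in any phase, but the PK schedule treats 30 minutes as the end of infusion, so a longer infusion on D1 or D15 loses early post-infusion samples and gives a Cmax that is not comparable

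*Protocol*

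**What the plan says.** **Administration.** Section 5.4 states: "The administration volume is 50 mL, and the infusion time is 30 minutes". It adds "The actual infusion time will be recorded" and then permits changes on safety and tolerability grounds: "adjustments to the drug concentration, infusion rate, infusion time, and administration volume will be made as necessary". The synopsis (preparation and method of administration) says that "adjustments may be made to the drug concentration, infusion rate, infusion time, and infusion volume", and ties this to the individual: "infusion rate, infusion time, and infusion volume based on individual subject safety and tolerability". Neither place limits the permission to the extended treatment phase or caps the change. Section 3.2.5 bars dose escalation in the single-dose and multiple-dose phases but does not mention infusion time or rate. Section 3.1 describes the D1 infusion as finished within 30 minutes.

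**Sampling.** Section 7.2.2 sets the D1 and D15 samples in time after administration, including "30 minutes (immediately after administration), 32 minutes, 35 minutes, 45 minutes, 1 hour", then 2, 4, 8 and 12 hours. The synopsis and sections 6.2 and 6.3 repeat this, and the sampling flowchart uses the same clock times. Section 7.2.1 uses actual sampling times in the AUC calculation for samples taken outside their window.

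**Analysis.** Under section 10.5 the single-dose parameters are "analyzed with a power function model to examine the relationship between AUC, C_max_, and dose". Accumulation compares multiple-dose with single-dose Cmax and AUC.

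**DLT and MTD.** Section 3.2.4 makes a subject evaluable on at least 80% of the planned dose, or on a DLT. Section 3.5 defines the MTD by dose and DLT count. Neither mentions infusion duration.

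**The concern.** The labels of the sampling schedule hold only if the infusion stops at 30 minutes. The cluster at 30, 32, 35 and 45 minutes is there to catch the peak and the first fall after it. When an infusion is lengthened, those draws describe the rising part of the curve instead. Samples that were never taken after the true end cannot be recovered at the analysis stage.

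Cmax after a constant-rate infusion also depends on how long the infusion lasted. A power model of Cmax on dose alone attributes a duration effect to dose. A D15/D1 Cmax ratio attributes it to accumulation, or hides accumulation, whenever the two infusions in the same subject differ in length.

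A separate question concerns the escalation decision. A subject whose infusion is slowed between D1 and D25 can still receive the full dose and so remain evaluable. The protocol does not say whether such a subject informs the dose level in the same way as the others.

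**Working it through.** The protocol gives no figure of its own on this point. The check first places the samples and then sizes the Cmax effect.

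**1. Where the scheduled samples fall for longer infusions** (schedule from section 7.2.2; durations other than 30 minutes are assumptions)

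- 40 min: the 30, 32 and 35 min samples are mid-infusion; no sample at the end; first decline sample at 45 min (+5).
- 45 min: 30, 32 and 35 are mid-infusion; the 45 min sample is at the end; next at 1 h (+15).
- 50 min: 30, 32, 35 and 45 are mid-infusion; no sample at the end; next at 1 h (+10).
- 60 min: 30, 32, 35 and 45 are mid-infusion; the 1 h sample is at the end; first decline sample at 2 h (+60).
- 90 min: every sample from 30 min to 1 h is mid-infusion; no sample at the end; next at 2 h (+30).

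A missed end matters little for small changes. Over assumed half-lives of 5 to 60 minutes, the highest observed value is 0-8% low at 40-50 minutes and up to 23% low at 90 minutes. For the last figure, with a 60-minute half-life, the 1 h sample against the 90-minute peak is (1 - 0.500)/(1 - 0.354) = 0.500/0.646 = 0.77.

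**2. Cmax for the same dose over 60 instead of 30 minutes**

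In a one-compartment model with constant-rate infusion, Cmax is proportional to (1 - exp(-kT))/(kT). The ratio for T = 60 against T = 30 minutes is

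[(1 - exp(-60k))/60] / [(1 - exp(-30k))/30] = (1 + exp(-30k))/2,

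so it cannot fall below 0.5. The protocol text gives no human k, so the animal values span the range (sections 1.4.3 and 3.2.2):

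- Rat half-life 3.79-6.24 min: ratio 0.50-0.52.
- Dog CL/Vdss: 68.4/3690, 73.4/3850 and 71.5/2890 give k = 0.0185, 0.0191 and 0.0247 per min; ratios 0.79, 0.78 and 0.74.
- Mouse plasma half-life 1.21 h: ratio 0.88.
- Dog terminal half-life 4.49-8.47 h: ratio 0.96-0.98.

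True AUC equals dose/CL under linear kinetics, whatever the duration.

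**3. Effect on the power-model slope**

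Use the seven planned doses of Table 7 (1.2, 2.4, 4.0, 6.0, 8.4, 11.2 and 15 mg/m²), equal group sizes and a true slope of 1. The mean log dose is 1.641 and the sum of squares about it is 4.778. The two highest doses have centred log values 0.775 and 1.067, sum 1.842. If every subject in those two groups has Cmax multiplied by r, the fitted slope is

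1 + (1.842/4.778) × ln r = 1 + 0.385 × ln r.

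- Assumed half-life 5 min, r = 0.508: 1 + 0.385 × (-0.677) = 0.74.
- Assumed half-life 60 min, r = 0.854: 1 + 0.385 × (-0.158) = 0.94.
- Dog CL/Vdss, r = 0.74-0.79: 0.88-0.91.
- Dog terminal half-life, r = 0.96-0.98: about 0.99.

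If only one subject in three is slowed in each of the two groups, the shift is a third as large. The range 0.74-0.94 then becomes 0.91-0.98.

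**4. Effect on the accumulation ratio**

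If D1 runs 30 minutes and D15 runs 60 minutes in the same subject, with no true accumulation, the D15/D1 Cmax ratio equals the step 2 ratio: about 0.5, 0.74-0.79 or 0.96-0.98, depending on disposition.

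**The case against.** Several counter-arguments stand.

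- **Dose proportionality uses D1 data only.** A subject has no tolerability history before the first dose. D1 is therefore prolonged only by a reaction during that infusion, or if later subjects are started more slowly. Changes prompted by experience act mainly on D15.
- **Whole top groups slowed is an extreme case.** A reader might infer that slowing will cluster at the highest doses and so bend the dose-Cmax relation. That is plausible, but nothing in the protocol documents it.
- **A large effect is not shown.** With one slow phase of 4-8 hours, as in the dog terminal half-life, the Cmax change is 2-4%.
- **The peak is not always lost.** Infusions of 45 or 60 minutes still have a sample at their end.
- **Some of this is covered or deferred.** Infusion time is recorded, actual sampling times enter AUC, and section 10.8 leaves detailed methods to the statistical analysis plan. The handling of unusual infusions in the Cmax analyses could properly be set there.

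A reader might also infer that the MTD definition contradicts the infusion rule, or that slowed subjects must be struck from the DLT-free count. The documents do not support either reading. Section 3.5 names a dose and no infusion length, so this is silence rather than contradiction. Striking subjects would be a new escalation rule with a replacement cost, and section 3.2.4 conditions evaluability on dose received or a DLT.

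What these arguments do not remove is the sampling problem. The draw times are fixed in the protocol. Neither recording the infusion time nor using actual times for AUC supplies early-decline samples that were never taken, or makes Cmax from different durations comparable.

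**Conclusion.** The point holds for the PK schedule and the Cmax comparisons. Followed as written, an infusion longer than 30 minutes on D1 or D15 leaves the early decline poorly sampled; at 60 minutes the first decline sample is at 2 hours. It may miss the peak, and it feeds a Cmax of different meaning into the power model or the D15/D1 ratio.

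The size in humans is unknown. The one-compartment range for a 60-minute infusion runs from about half the 30-minute Cmax to almost no change, depending on how fast early disposition is. Slopes of 0.74-0.94 need assumed half-lives of 5-60 minutes and every subject in the top two groups slowed on D1, so they mark an upper end and are not an expectation. Under linear kinetics true AUC is unaffected.

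For DLT and MTD, the supportable conclusion is narrower: the protocol leaves open whether infusion changes are allowed in D1-D25 and how affected subjects count.

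**What to change.** 1. **Sampling.** In section 7.2.2, and to match in the synopsis, sections 6.2 and 6.3 and the sampling flowchart, define the end-of-infusion and following early samples relative to the actual end of infusion: end, +2, +5, +15 and +30 minutes. For a 30-minute infusion these are the present 30, 32, 35, 45 and 60 minute samples, so nothing changes for a subject on the planned schedule.
2. **NCA.** Use the recorded infusion duration for each subject and dosing day.
3. **Cmax analyses.** In section 10.5, base Cmax dose proportionality and the Cmax accumulation ratio on infusions of the planned length, or show them with and without the others. Keep AUC for all subjects.
4. **Reconcile.** Bring section 5.4 and the synopsis into line with sections 3.2.4, 3.4 and 3.5: state whether infusion time or rate may change in D1-D25 and how such subjects count for DLT and MTD. No particular clinical rule is proposed here.

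Items 1 to 3 cost wording only, since infusion time is already recorded. The downside is that a few subjects may leave the Cmax analyses, which matters with 3-6 per group; showing both versions limits that loss. The cost of item 4 depends on the rule the sponsor chooses.
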